***Child measures***				

Temperamental inhibition	Short Temperament Scales - Inhibition subscale [47]	Screening	7	Children who score ≥85^th ^percentile are eligible for the trial.

Major health or developmental diagnoses	Parents' Evaluation of Developmental Status (Australian version)[53]	RCT baseline	10	Children with major diagnoses will be excluded: determined on a case-by-case basis.

Behavioural and emotional problems	Strengths & Difficulties Questionnaire (4-10 year old Australian version)[54]	Screening 1 & 2 years	25	Behavioural screening measure; widely used in population health research; existing school-entry screen in Victoria. Emotional subscale may have concurrent validity with temperamental inhibition screen. Secondary outcome (impact on externalising/conduct problems).

Anxiety diagnoses	Anxiety Disorders Interview Schedule for DSM-IV, Child Version, Parent Interview Schedule (ADIS-CP-IV) [55]	1 & 2 years		Primary outcome. Conducted by telephone interview.

Internalising problems	Children's Moods, Fears and Worries Questionnaire [1]	1 & 2 years	34-38	Primary outcome. Detailed measure of internalising symptoms (anxious, fearful, withdrawn, depressive) in young children.

Anxiety problems	Preschool Anxiety Scale - Revised (PAS-R)[56]	1 & 2 years	28	Primary outcome. Detailed measure of anxiety symptoms in young children. Sensitive to intervention in *Cool Little Kids *efficacy trial.

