### Rationale for the proposed *Cool Little Kids *population-level study

The strongest precursor of internalising problems in young children is temperamental inhibition, manifested as fearfulness and a tendency to withdraw from new situations [29,31-34]. Additional known risks are harsh and overprotective parenting, and parent internalising problems [9,10,34-39]. Together, these account for up to 45% of the variance in early childhood internalising symptoms [9,10,35].

The only randomised trials testing a parenting prevention model in inhibited preschool children were conducted by [name]. [name]'s *Cool Little Kids *program is the first (and, thus far, only) effective early childhood prevention program for internalising disorders [30,40-42]. Targeting child inhibition and overprotective parenting, this parenting program aims to help preschool children become resilient to situational fears and abstract distressing worries. It teaches parents strategies to modify their preschool child's fear and distress, as well as their own (if relevant), based on standard principles for treating internalising disorders in children and adults [11,42].

Two successful efficacy trials of the *Cool Little Kids *program have been reported. [name]'s first trial [41] recruited 146 children aged 4 years with temperamental inhibition, measured by parent-report questionnaire (>85th percentile) and intensive laboratory observation. Intervention parents received a university-based prevention program from teams of two clinical psychologists offering six group sessions designed to reduce overprotective parenting in response to early fearful behaviour. By age 5 years, the intervention children had developed significantly fewer anxiety disorders than controls (50% vs. 64%). These effects were even larger by age 7 (40% vs. 69%) [42]. [name]'s second study [40] recruited 71 inhibited preschoolers whose parents themselves had internalising disorders. The intervention group received an eight-session version of the program which extended to focus on parent anxiety as well as overprotective parenting. Six months later, the intervention children had substantially fewer internalising disorders, diagnosed in only 53% of the intervention group compared to 93% of controls.

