### Aims and hypotheses

The aims of this trial are to (a) determine the balance of benefits and harms of systematically screening preschoolers for temperamental inhibition and of a parenting intervention program offered to those at risk, (b) examine the impacts on child internalising problems at school entry, and (c) evaluate cost-effectiveness.

We hypothesise that children whose parents enter the program will do better one and two years after baseline (the first two years of school for most) than 'usual care' control children on the outcomes: i) fewer children with internalising disorders, ii) lower mean scores on early child internalising symptoms, iii) lower mean scores on harsh and overprotective parenting, iv) lower mean scores on parent internalising problems. We anticipate that the prevention program will be acceptable and cost-effective.

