### Sample size

The randomised trial will have a sample size of around 500 inhibited children, providing 80% power at the 5% level of significance to detect the level of reduction in internalising problems found in [name]'s prior efficacy trials, namely a 14% reduction in child internalising disorders between the intervention (50%) and control (64%) groups [41]. This sample size estimation considers an achievable attrition rate for a quality trial, allowing for up to 20% loss to follow up.

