### Data analyses

Regression analyses will compare child outcomes and costs at school-entry (1 and 2 years after baseline) between the intervention and control arms using the intention-to-treat principle, where participants are analysed in the groups to which they were randomised. Logistic regression will be used for binary outcomes (presenting the percentages for each trial arm and odds ratio between them) and linear regression for continuous outcomes (presenting the mean and standard deviation for each trial arm and mean difference between them). Both unadjusted analyses and analyses adjusted for potential confounding factors determined *a priori *before randomisation (child gender, family socioeconomic level, parent mental health) will be implemented. Tests of interaction, specified *a priori*, will explore differential intervention effects for children who are higher on risk factors at baseline. In line with [name]'s second efficacy trial [40], we anticipate larger group differences might emerge for children who are higher on risk factors at baseline.

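### Table 1 makes three measures primary at two time points, while the sample size allows for one disorder comparison at the full 5%

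*Protocol article*

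**What the plan says.** In the child section of Table 1, three instruments carry the primary label, each scheduled at 1 and 2 years:

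- ADIS-CP-IV diagnosis: "Primary outcome. Conducted by telephone interview"
- Children's Moods, Fears and Worries Questionnaire: "Primary outcome. Detailed measure of internalising symptoms (anxious, fearful, withdrawn, depressive) in young children"
- PAS-R: "Primary outcome. Detailed measure of anxiety symptoms in young children"

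Aims and hypotheses expects that intervention children "will do better one and two years after baseline", and lists disorders and symptom scores as separate hypotheses without ranking them. Data analyses says: "Regression analyses will compare child outcomes and costs at school-entry (1 and 2 years after baseline) between the intervention and control arms". It plans both unadjusted and adjusted models and does not say which is the main one.

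Sample size rests on one comparison, "a 14% reduction in child internalising disorders between the intervention (50%) and control (64%) groups", with about 500 children "providing 80% power at the 5% level of significance" and up to 20% loss. It names no time point. The two rates come from the first efficacy trial, described in the Rationale: "the intervention children had developed significantly fewer anxiety disorders than controls (50% vs. 64" (percentages, by age 5, in children recruited at age 4).

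**The concern.** Three measures at two years make six comparisons of equal standing, and the sample size supports one of them. The two questionnaires have no target difference, standard deviation or power.

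Two things are at stake. First, if each comparison is tested at 5%, an ineffective programme has well over a 5% chance of producing some significant primary result. Second, a mixed result has no agreed reading, and one is foreseeable. A clinician blind to allocation assigns the diagnosis, whereas parents who know their allocation complete the questionnaires. The questionnaires could favour the programme while the diagnosis does not. The Discussion says that large-scale rollout is appropriate if the programme proves effective, but not which outcome or year decides that.

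**Working it through.** **1. Reproduce the planned N.** Inputs from Sample size: 64% and 50%, 5% level, 80% power, 20% loss. Assumptions: two-sided test, 1:1 allocation, pooled variance under the null, no continuity correction.

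- Mean rate = 0.57; √(2 × 0.57 × 0.43) = 0.7001; √(0.64 × 0.36 + 0.50 × 0.50) = 0.6931
- n per arm = (1.960 × 0.7001 + 0.842 × 0.6931)² / 0.14² = 195.1, rounded up to 196
- Total = 392; 392 / 0.80 = 490, against about 500 stated

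So the plan reproduces as one unadjusted two-proportion comparison at the full 5%. With a continuity correction the total would be 525.

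**2. Count the primary comparisons.** 3 instruments × 2 years = 6. Counting unadjusted and adjusted models separately gives 12, but the two versions of one test are closely related, so six is used below.

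**3. Chance of at least one false positive, each test at two-sided 5%.**

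- Six independent tests: 1 − 0.95⁶ = 26.5%. The ceiling under any dependence is 6 × 5% = 30%.
- Three independent tests (one year): 1 − 0.95³ = 14.3%.

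For correlated tests I simulated normal test statistics with one common correlation:

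| Assumed correlation | Six tests | Three tests, one year |
|---|---|---|
| 0.5 | 20.7% | 12.5% |
| 0.6 | 18.6% | 11.8% |
| 0.7 | 16.5% | 10.9% |
| 0.8 | 13.8% | 9.8% |
| 0.9 | 10.8% | 8.4% |

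I also let the correlation differ between instruments and between years, taking the product of the two for different instruments in different years:

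| Between instruments | Between years | Six tests |
|---|---|---|
| 0.6 | 0.55 | 20% |
| 0.8 | 0.7 | 16% |
| 0.9 | 0.63 | 14% |
| 0.9 | 0.9 | 12% |

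The between-year values of 0.55 and 0.63 have some support: the Background reports stability of internalising symptoms of r = .53 to .63. The between-instrument values are assumptions, as the article gives none.

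**4. Cost of keeping several primaries.** With 200 per arm after 20% loss, power for 64% vs 50% is Φ[(0.14 × √200 − z × 0.7001) / 0.6931], where 0.14 × √200 = 1.980.

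| Level for the diagnosis | z | Power | N for 80% power, with 20% loss |
|---|---|---|---|
| 0.05 (one test) | 1.960 | 81.0% | 490 |
| 0.05/3 = 0.0167 | 2.394 | 66.9% | 653 |
| 0.05/6 = 0.0083 | 2.638 | 57.6% | 755 |

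**5. The questionnaires.** With 200 per arm, the difference detectable with 80% power at 5% is (1.960 + 0.842) × √(2/200) = 0.28 SD. The article does not say whether such a difference is expected or would matter.

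**The case against.** The best defence is that this is a journal article. Control of the error rate is commonly left to an analysis plan, which is not shown here, so its absence cannot be held against the article. That is right, and it limits the point: no complaint is made that a multiplicity method is missing. What stands is that the article itself assigns primary status, to three measures at two years, and bases its sample size on one comparison.

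Four stronger readings are tempting and are not supported:

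- *The plan allows success to be claimed on any one of six results.* A reader might infer this, but no success rule is written. The 5% level appears only under Sample size, so its use for every test is an inference.
- *The false-positive rate is 26%.* That figure assumes independence, which is implausible for overlapping parent-based measures of the same children.
- *The questionnaires are underpowered.* Nothing shows this. They lack a stated justification, and 0.28 SD would be detectable.
- *The article contradicts itself on the powered endpoint.* The Rationale and Table 1 speak of anxiety, while Sample size and Outcome measurement speak of internalising. The Background defines internalising problems to include anxiety and depression, so an anxiety disorder is an internalising disorder and the labels are compatible. The one open question is whether mood diagnoses count.

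**Conclusion.** The point holds as a mismatch between the outcome table and the sample size: six comparisons are designated primary, and one is sized, at the full 5%. If each is tested at 5%, the chance of at least one false-positive primary result is 26% under independence. It is about 11% to 21% at a common correlation of 0.9 down to 0.5, and about 12% to 20% when the correlations between instruments and between years are set separately. Restricting the count to one year leaves about 8% to 14%. The exact value depends on correlations that the article does not give, but it exceeds 5% throughout these ranges.

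The planned N itself is sound for one ADIS comparison, at either year. The defect lies in the designation and can be corrected without enlarging the trial.

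**What to change.** 1. Name one primary outcome at one time point in Table 1, Aims and hypotheses, and Sample size. The ADIS diagnosis is the measure the trial is sized for. One year is the closest match to the planning rates, which follow children from age 4 to age 5; this is a reasoned choice, as the article names no year.
2. Make the diagnosis at the other year and both questionnaires secondary.
3. State in advance whether the unadjusted or the adjusted model is the primary one. The article does not settle this. The sample size reproduces as an unadjusted comparison, but that does not oblige the choice.
4. As a minor point, state whether mood diagnoses count towards the powered endpoint.

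The cost is rewording, with N still near 500. The downside is that the two questionnaires lose primary status.

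If several primaries are preferred, state the multiplicity rule and restate the power. Where the diagnosis has to pass the strictest step, its power with 200 per arm falls from 81% to about 67% for three tests or 58% for six. Restoring 80% at that step would take about 653 or 755 children.

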## Background

Few people in modern societies are untouched by internalising problems, a broad term that refers to emotional distress and encompasses the spectrum of emotional symptoms of anxiety and depression. Although in clinical practice anxiety and depression disorders are seen as multiple, distinct diagnoses, empirical evidence shows high overlap between them and supports use of the broad term internalising problems [1,2]. The World Health Organization (WHO) predicts that, by 2030, internalising problems will be second only to HIV/AIDS in burden of disease [3].

Mental health problems affect 1 in 7 school aged children [4], although they can occur in children of all ages. Internalising (emotional) and externalising (behavioural) problems are among the most common difficulties of early childhood, affecting approximately 15% of those aged 18 months to 5 years [5-8]. Australian community studies have recently confirmed this high prevalence and stability of internalising symptoms across early to mid childhood (e.g. Pearson r's = .53 to .63) [9,10]. By the time internalising disorders are detected problems can be severe and treatment effectiveness can be limited [11,12].

Early internalising problems often have longer-term consequences, with many adult problems having early roots in childhood [4,13,14]. Convergent evidence from prospective and retrospective studies confirms that internalising problems often persist into adolescence and then into adulthood [4,15-24]. Their impacts extend beyond mental health to adult relationships, employment opportunities, and even early mortality. For example, in the British National Child Development Study (N = 11,142), internalising problems at ages 7-11 years were predictive of higher mortality by age 45 (OR 1.20, 95% CI 1.06-1.35) [21].

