***Intervention 'process' measures***				

Fidelity	Group sessions content checklists, rated by facilitator and researcher	6 month appraisal	6-8	Secondary outcome (integrity of intervention delivery). Adapted for this study.

Acceptability to parents	Perceptions of screening process Perceptions of group sessions content, group facilitator	6 month appraisal	4 15	Secondary outcome (implications for translation/dissemination uptake by families). Adapted for this study.

Cost-effectiveness	Child and adult health service use	1 & 2 years	6	Secondary outcome (for policy/decision makers considering translation/dissemination). Generated for this study.

After scoring, the study team will notify parents by letter if their child does not score highly on temperamental inhibition and is therefore ineligible for the trial. Eligible parents will be mailed the detailed trial Information Statement and Consent form with the baseline questionnaire ascertaining family risk for internalising problems and more detailed demographic characteristics (see Table 1). The study team will also telephone all eligible parents to explain trial procedures in detail and answer parents' questions.

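### The two primary symptom scales have no baseline measurement and the planned covariates include no child symptom score, so some precision is given up

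*Protocol article*

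**What the plan says.** Table 1 of the protocol article gives each measure its time points. The two symptom scales are listed as "Preschool Anxiety Scale - Revised (PAS-R)[56] 1 & 2 years 28" and "Children's Moods, Fears and Worries Questionnaire [1] 1 & 2 years 34-38". Their notes read "Primary outcome. Detailed measure of anxiety symptoms in young children" and "Primary outcome. Detailed measure of internalising symptoms (anxious, fearful, withdrawn, depressive) in young children". Other rows of the same table carry a screening or baseline time point, so the absence of one here is a stated schedule and not an effect of condensing the protocol into an article.

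Two child scores do exist before randomisation: the inhibition subscale of the Short Temperament Scales, and the SDQ with its emotional subscale, which Table 1 places at screening and again at 1 and 2 years.

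A mailed form also exists before randomisation. Under Recruitment and participants (in the text after Table 1): "Eligible parents will be mailed the detailed trial Information Statement and Consent form with the baseline questionnaire ascertaining family risk for internalising problems". Allocation follows consent. The follow-up symptom scales are themselves collected by mailed parent questionnaire (Outcome measurement).

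Data analyses plans linear regression for continuous outcomes, both unadjusted and adjusted, with the adjustment set "child gender, family socioeconomic level, parent mental health) will be implemented". The Background reports "stability of internalising symptoms across early to mid childhood (e.g. Pearson r's = .53 to .63".

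**The concern.** A score on the same scale before randomisation is usually the best single predictor of the later score, and adjusting for it narrows the confidence interval for the difference between arms. Here the secondary parent outcomes (parenting practices, parent mental health) get a baseline value, but neither symptom scale named as primary does. The child scores that are collected at screening are not in the adjustment set.

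An unseen analysis plan could still add the screening scores as covariates. It could not recover a PAS-R or CMFWQ score that was never collected before randomisation, so that part has to be settled in the protocol. At stake is how small a difference in mean symptom scores the trial can resolve with the children it follows.

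**Working it through.** **1. The plan's own sample size.** Inputs from Sample size: 64% versus 50% with a disorder, 80% power, 5% level, up to 20% loss. Two-sided testing and 1:1 allocation are assumed. The mean of the two rates is 0.57.

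n per arm = [1.960 × √(2 × 0.57 × 0.43) + 0.842 × √(0.64 × 0.36 + 0.50 × 0.50)]² / 0.14² = 196 after rounding up.

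196 / 0.80 = 245 per arm, or 490 in total. The stated figure of around 500 is reproduced. It rests on the binary diagnosis and is not in question.

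**2. Effect of a same-scale baseline in a linear model.** 500 less 20% leaves 400, or 200 per arm. With no covariates, the difference detectable with 80% power is (1.960 + 0.842) × √(2/200) = 0.280 SD. This 0.280 SD is a reference point only; the protocol states no effect size for either scale. Adjusting for a baseline with correlation r multiplies the residual variance by 1 − r².

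| r | Source | 1 − r² | Variance removed | Detectable difference at 80% power | Equivalent analysed N (400 / (1 − r²)) | Power at 0.280 SD |
|---|---|---|---|---|---|---|
| 0 | no baseline | 1.00 | 0% | 0.280 SD | 400 | 80% |
| 0.30 | assumption | 0.91 | 9% | 0.267 SD | 440 | 84% |
| 0.53 | Background | 0.72 | 28% | 0.238 SD | 556 | 91% |
| 0.63 | Background | 0.60 | 40% | 0.218 SD | 663 | 95% |

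**3. Effect of selecting on inhibition.** The trial takes children at or above the 85th percentile. Under normality, the variance of the inhibition score among them is 0.195 of its population value, so k = 1 − 0.195 = 0.805. Let inhibition correlate c with the baseline scale and y with the outcome. The correlation within the trial is then (r − c·y·k) / √[(1 − c²k)(1 − y²k)]. With assumed c of 0.3 to 0.7 and y of 0.3 to 0.5, the values 0.53 to 0.63 become about 0.36 to 0.62, or 13% to 38% of variance. The r of 0.30 in the table is a more cautious assumption than this range.

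**4. What the scores already collected could do.** The protocol gives no correlations, so all of these are assumed.

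- *Inhibition score.* Within the selected sample it explains y² × 0.195 / (1 − y² × 0.805) of the outcome variance. For y = 0.3 this is 0.0176 / 0.928 = 2%; for y = 0.5 it is 0.0488 / 0.799 = 6%. Selection limits its value.
- *SDQ emotional score.* Let it correlate s = 0.3 to 0.5 with the outcome and ρ = 0.5 to 0.7 with the baseline scale. Alone it removes s², that is 9% to 25%. With both scores in the model, R² = (r² + s² − 2rsρ) / (1 − ρ²), and the remaining variance relative to SDQ alone is (1 − R²) / (1 − s²). At r = 0.53 to 0.63, ignoring selection, the same-scale baseline then removes a further 9% to 38%.

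**5. Burden.** Table 1 items on the baseline form: 10 + 32 + 8 + 21 + 12 = 83, before demographics. The PAS-R adds 28 / 83 = 34%, making 111. Both scales add 62 to 66 items (75% to 80%), making 145 to 149. The follow-up instruments total 28 + (34 to 38) + 25 + 40 + 21 + 35 + 6 = 189 to 193 items.

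**The case against.** The case against is substantial.

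- **Nothing is invalid.** The hypotheses concern lower mean scores at one and two years, and a randomised comparison of those means is sound. Chance imbalance in starting symptoms is already reflected in the confidence interval. This stands: the point is about efficiency only.
- **Adjusted models are planned.** A reader might infer that the two scales will be compared with no adjustment at all. Data analyses does not support that. Parent mental health is in the set, and the Background lists parent internalising problems among risks that together explain up to 45% of variance in early childhood internalising symptoms. The 28% to 40% is measured against a model with no covariates, so it is not the gain over the planned one. This stands.
- **The correlations may not carry over.** They come from community studies. The article gives neither the instrument nor the interval, and the trial sample is selected on inhibition. This stands, and is why the lower figure belongs beside the upper ones.
- **The power figures are illustrative.** A reader might infer that the continuous outcomes are underpowered. The protocol sets no target difference for them, so that cannot be shown.
- **Length has a price.** The baseline form travels with the consent form, so a longer one could cost enrolment as well as item response, and 490 needed against about 500 planned leaves little slack. This stands most strongly against adding both scales. It carries less weight for the PAS-R alone, since 111 items is still well below what is asked at follow-up. It does not touch the use of scores already collected.

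**Conclusion.** The point holds as an avoidable loss of precision on the two continuous primary outcomes. It is neither a bias nor a fault in the stated sample size.

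Relative to an unadjusted model, a same-scale baseline would remove about 9% of residual variance if r is 0.30 in the selected sample (assumed), and at most 28% to 40% if the community-sample r of 0.53 to 0.63 applied unchanged. The gain over the planned adjusted model should be smaller, because the planned covariates probably explain part of the same variance; the document does not allow it to be computed. A reader might take the upper figures as the loss the trial will suffer, but they are a ceiling resting on correlations from another kind of sample.

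The case for change does not depend on the upper figures. One part of the remedy needs no new data, and the other needs 28 items on a form already mailed.

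**What to change.** 1. **Data analyses:** add the screening SDQ emotional score and the screening inhibition score as prespecified covariates in the adjusted models for the child outcomes, and keep the planned unadjusted analyses beside them. This needs no new data. For the diagnosis, state that the adjusted odds ratio is conditional on the covariates; the variance figures above apply only to the linear models.
2. **Table 1 and Recruitment and participants:** add the PAS-R to the baseline questionnaire mailed before randomisation, and enter that score as a covariate in the 1- and 2-year PAS-R models. The cost is about one third more items on a form of about 83 that goes out with the consent form, with possible small effects on item response and enrolment. No visit or interviewer is added.
3. **Optional:** add the CMFWQ as well and use it in the same way. With both scales the form grows by about three quarters or slightly more, so the sponsor should weigh this against enrolment. If it is left out, the screening SDQ emotional score serves as a partial substitute in the CMFWQ models.
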